### Monitoring

#### Data monitoring

A data monitoring committee will not be established as the overall risk associated with the trial is considered low, and therefore, the likelihood for the need to modify or discontinue the trial is considered insignificant. However, precautions have been taken to minimize the potential of any harms, as detailed below. Moreover, a detailed process evaluation will be conducted throughout the entire trial to produce in-depth insight into the delivery of the interventions, (i) to prevent drawing inappropriate conclusions on the efficacy or effectiveness of the interventions, and (ii) to formulate recommendations for future studies [68]. Most importantly, process evaluation should be used to identify and avoid potential burdens for study participants and GPs. The process evaluation will comprise three dimensions:Evaluation of the success rate of recruitment: Standardized questionnaires filled in by the GP personnel collecting number of eligible patients, number of participants and non-participants, baseline-characteristics of both groups, and reasons for non-participation. Loss of participants during the follow-up-period as well as reasons for leaving the study will be assessed to evaluate attrition rate as well as barriers and facilitators for staying in the trial [5].Evaluation of the quality of the execution of the intervention components: At every face-to-face or telephone interim session, adherence to the intervention will be assessed using standardized questionnaires with intervention A participants in order to identify potential barriers and facilitators for adherence to the intervention. Likewise, GPs will be asked to fill out a standardized questionnaire to identify potential burdens for participating GPs.Evaluation of the process of data acquisition regarding completeness and validity: Documentation of reasons for discontinuing an assessment before completion as well as the motivation of the participants and the GPs for assessment. Number and characteristics of missing data will be analyzed. Information will be used to evaluate barriers and facilitators for data collection.

### Harms

Trial-related adverse events (AEs) will be assessed without regard towards a causal relation to the intervention. AEs will be recorded at each contact with participants after the baseline assessment. AEs in *AgeWell.de* include loss experiences and grief, depressive symptoms, severe injuries, hospitalization, and private or occupational stress reported by participants. Specific AEs (depressive symptoms; severe injuries; hospitalization) will be considered serious adverse events (SAEs) if they result in a life-threatening condition (immediate risk or death), hospitalization/prolongation thereof, or any lasting impairment. Occurrence of AEs/SAEs will be documented in the electronic database after each contact with participants. In case of a SAE, an automatic case-report form will notify the coordinating study center at the University of Leipzig, which, in turn, will contact the respective study center. A shared decision will then be made between the coordinating study center and non-elective principal investigator (PI) at the respective study center, including one of the following options: informing the participants’ GP about the SAE, interruption or discontinuation of trial participation, or none of the above.

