At baseline and at follow-up assessment after 24 months, fully structured interviews will be conducted with all participants, assessing the primary and secondary endpoints. Other relevant information assessed include sociodemographic information, subjective cognitive decline, self-reported impairments and symptoms, anthropometry, blood pressure, nutrition, physical activity, bereavement/grief, medication, vascular risks). Moreover, GPs will provide data on participants’ health characteristics (diagnoses, lab values, medication) using standardized questionnaires. To conduct the process evaluation, the success rate of recruitment (number of eligible GP patients, number of participants and non-participants, (baseline) characteristics of participants and non-participants, reasons for non-participation) will be provided by the GP practice personnel. Standardized telephone interviews on reasons for dropout will be held with intervention A-participants, if applicable. For participants in intervention A, additional interim sessions will be scheduled: one face-to-face assessment after 12 months at the participants’ home and five telephone calls after 2, 4, 8, 16, and 20 months, respectively (see Table 3). These fully structured interviews serve the purpose of monitoring adherence to the intervention and motivation (monitoring & booster sessions). Participants in intervention group A will be asked to track their activities in the intervention components using weekly diaries. To reduce non-response as well as dropout in *AgeWell.de*, interviewers will undergo training regarding all procedures and assessments, including motivational interviewing techniques [64]. Likewise, motivational tasks will also be carried out by the principal investigators (Table 1).

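### Adverse events are elicited at seven scheduled contacts in arm A and one in arm B, so AE counts are not comparable as collected; dropout reasons are asked by interview in arm A only, although another section implies both arms

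*Protocol article*

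**What the plan says.** **Recording rule.** Under Harms, "AEs will be recorded at each contact with participants after the baseline assessment". The events are defined as "loss experiences and grief, depressive symptoms, severe injuries, hospitalization, and private or occupational stress reported by participants". They are recorded whether or not they are thought to be caused by the intervention.

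**Contacts.** Under Data collection, "At baseline and at follow-up assessment after 24 months, fully structured interviews will be conducted with all participants". The text then adds: "For participants in intervention A, additional interim sessions will be scheduled". These are "one face-to-face assessment after 12 months" and "five telephone calls after 2, 4, 8, 16, and 20 months". The footnotes to Table 3 likewise tie the telephone sessions and the 12-month visit to arm A. No interim contact is described for arm B.

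**Reasons for leaving.** Data collection states: "Standardized telephone interviews on reasons for dropout will be held with intervention A-participants, if applicable". The process-evaluation part of Table 2 lists the same instrument with the same restriction. The Data monitoring section, describing the same process evaluation, plans to assess losses and the reasons for them without limiting this to one arm.

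**The concern.** The recording rule reads the same for both arms, but it is tied to a contact schedule that differs between them. Grief, stress, low mood and injuries are reported by the participant, so how many are recorded depends on how often and how soon people are asked. Arm A is asked every 2 to 4 months. Arm B is asked once, about the preceding two years. An arm A participant who leaves after month 8 has already been asked three times. An arm B participant who leaves before month 24 has never been asked.

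Because AEs are recorded without regard to cause, the control arm is the natural reference for reading them. If the counts are set side by side, closer observation can pass for harm in arm A. Equally, a real excess there, for example of injuries in an arm with an exercise component, can be put down to closer observation. Interviewers and study nurses are not blinded (Blinding), which gives no protection against this.

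The arm-A-only dropout interview raises a smaller, related point. Reasons for leaving help to judge whether loss to follow-up is related to cognitive decline, and two parts of the article disagree on whether they are sought in arm B.

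**Working it through.** **1. Count of scheduled contacts (Data collection).** The article gives the schedule but no total.

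- Arm A: 5 calls + 1 visit at month 12 + 1 follow-up at month 24 = 7. Gaps: 2, 2, 4, 4, 4, 4, 4 months; longest 4.
- Arm B: 1 follow-up at month 24. Gap: 24 months.

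The body of Table 3 was not available for this check, so the count rests on the text and the table's footnotes. Contacts initiated by arm A participants, which Table 1 encourages, would come on top.

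**2. Average delay between an event and the next question.** For an event at a uniformly distributed time, the mean delay is Σ(g²/2)/24 over the gaps g.

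- Arm A: (2 × 4 + 5 × 16)/2/24 = 44/24 = 1.8 months.
- Arm B: (24²/2)/24 = 12 months.

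**3. Effect on recorded counts at equal true rates.** The documents give no recall rates, so this is an illustration. Assume that an event is reported at the next contact with a probability that halves every h months, and that nobody drops out. With k = ln 2/h, the share of events recorded is Σ[(1 − e^(−kg))/k]/24.

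| Assumed half-life h (months) | Recorded, A | Recorded, B | Ratio A:B |
|---|---|---|---|
| 6 | 0.816 | 0.338 | 2.4 |
| 12 | 0.901 | 0.541 | 1.7 |
| 24 | 0.949 | 0.721 | 1.3 |
| 60 | 0.979 | 0.873 | 1.1 |

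Example for h = 6, k = 0.1155. In arm A, the two 2-month gaps give 2 × 1.786 and the five 4-month gaps give 5 × 3.203, together 19.59; 19.59/24 = 0.816. In arm B, (1 − 0.0625)/0.1155 = 8.12, and 8.12/24 = 0.338. The ratio is 0.816/0.338 = 2.4.

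The size moves with the assumption, but the ratio exceeds 1 throughout. The model leaves out repeated asking about recurring states such as stress, and arm B dropouts who are never asked. Both push the same way.

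**4. Participants affected by dropout (Sample size).** At the assumed ceiling of 10%, 576 × 0.10 = 57.6, so at most about 58 arm B participants would have no AE contact after baseline and no dropout-reason interview.

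**5. Dropout reasons, side by side.** Data collection and Table 2 name a single instrument and restrict it to arm A. Data monitoring plans to assess reasons for leaving with no restriction, and no instrument is named that would do this in arm B. The passages need reconciling.

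**The case against.** **No between-arm AE test is promised.** The Harms section describes monitoring: recording, notification of serious events and a decision on the participant. How AEs are tabulated may be settled in an analysis plan that is not shown, and closer contact with the arm receiving the active programme is a defensible monitoring choice. This stands as far as it goes: the fault lies in how events are ascertained, not in a stated analysis. But the unequal ascertainment is a stated rule, and no later analysis can recover arm B events that were never elicited.

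**A reader might infer that neither harms nor attrition can be compared.** The article does not support that. Both arms have the same 24-month follow-up, so dropout rates are comparable; only the reasons are collected unequally. Mortality, nursing home placement, depressive symptoms (GDS) and health care use (FIMA) are outcomes in both arms.

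**A reader might infer that nothing is known about arm B participants who leave.** That is too strong. Table 2 takes mortality from the GP or a confidant, and nursing home placement from the GP or a contact person when the participant is unavailable. What is lost is the participant-reported AE record.

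**A reader might infer that the missing-data and selection-bias checks are one-sided.** They are not, as written. The dropout analysis under Statistical analyses compares complete and incomplete cases on sociodemographic variables, which are collected at baseline in both arms, and does not rely on the dropout interview. Data monitoring also plans to analyse the number and characteristics of missing data without an arm limit.

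**The magnitude is assumed.** This is correct. The direction follows from the schedule; the size does not.

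**Conclusion.** The point holds in this form. AEs are elicited at seven scheduled contacts in arm A and one in arm B, so AE and SAE counts are not comparable between arms as collected and lean towards more recorded events in A. The contact counts come directly from the article. The direction assumes only that recall fades or that repeated asking brings out more reports. The size, about 1.1 to 2.4 times, rests on assumed recall half-lives of 60 to 6 months and is not an estimate for this trial. Hospitalizations are probably remembered better than stress or low mood, so the distortion is likely to differ by event type.

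The restriction of the dropout-reason interview to arm A is a separate, smaller point: an inconsistency with the Data monitoring section, affecting at most about 58 arm B participants at the assumed dropout ceiling. The planned comparisons of attrition rates and of the symmetrically measured outcomes are unaffected.

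**What to change.** 1. Base any between-arm harms comparison on identical AE and SAE questions with the same look-back period, asked of both arms at the 24-month interview.
2. Support it with the outcomes already collected in both arms: mortality, nursing home placement, GDS, and health care use from FIMA, including hospital use where recorded.
3. Keep recording AEs at the arm A interim contacts for monitoring, but report them separately and descriptively.
4. Reconcile Data monitoring with Data collection and Table 2 by collecting reasons for leaving in the same way in both arms.

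**Cost.** A few case-report-form items at month 24 and at most about 58 short calls in arm B, using the interview that already exists. The treatment programme is unchanged.

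**What it does not solve.** The common look-back gives up some detail in arm A. Long recall still under-counts events in both arms. Arm A participants have been asked before, so their recall at month 24 may still be somewhat better. Participant-reported AEs in people who drop out remain uncaptured.

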**Fig. 1 Fig1:**
[figure not shown]
Study aims and hypotheses of AgeWell.de

On the one hand, our study will be guided by the FINGER trial by including the components nutritional counseling, physical activity enhancement, cognitive training, and vascular risk monitoring in the 2-year intervention program. On the other hand, we aim to additionally include components of social lifestyle and recommendations on medication overuse and underuse. Encouraging participants to be socially active should also be a beneficial component of the intervention as even in old age an active lifestyle is protective against dementia [6, 18–20]. Likewise, we will provide specific recommendations on the medications of the study participants to their respective GP, if needed. German health claims data suggested that 22–25% of individuals aged 64 years and older receive at least one prescription of a potentially inappropriate medication (PIM) drug within one year [21, 22]. Primary data from a sample of community-dwelling people with dementia indicate that 22% receive at least one PIM with the highest prevalence being antidepressants, benzodiazepines and analgetics [23]. PIM constitutes a major public health concern especially in older age leading, for example, to an increased risk of adverse drug reactions, hospitalization, and mortality [24, 25]. Moreover, PIM is of particular importance as studies strongly suggest that specific drugs (e.g. with anticholinergic properties) can also increase the risk for dementia [13, 26, 27]. On the other hand, medication underuse can modify cardiovascular and other risks [28] and thus outcomes relevant for dementia development.

Finally, we will address further known risk factors for dementia by providing specific interventions in case of bereavement, grief, and depressive symptoms [29, 30], if necessary. The broad range of outcomes will additionally enable the estimation of total benefit and cost-effectiveness of the intervention suggested to be more beneficial for the intended outcomes. The study protocol describes the rationale and the study design of the AgeWell.de trial in adherence to the SPIRIT 2013 statement (Standard Protocol Items: Recommendations for Interventional Trials; [31]).

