Cognitive training	- Information on cognitive functioning and the impact of cognitive activity/training on cognitive performance and dementia risk; information on strategies to train cognition in everyday life - Cognitive training at home on a regular basis (3 times/week, 15 min per session) with tablet computers (software: NeuroNation; https://www.neuronation.com/)
Optimization of medication	- Collection of baseline information (i) from the GP on participants’ medication, diagnoses, and lab values (creatinine, hemoglobin A1c) and (ii) from the participants on their actual medication - Electronically supported data evaluation to identify potentially inappropriate medication (e.g. anticholinergics, using a list based on Gray and coworkers [13], potentially missing drugs (using START criteria A1 to A8; [34]), contraindicated drug combinations, and contraindications in patients with renal impairment (using databases from the electronic drug information system AiD*Klinik*). Discrepancies in the information on medication collected from the participant and the GP will be identified. - Reports including recommendations on the medication of a participant will be transmitted to the GP. For recommended drugs, this will include information on potentially serious drug-drug interactions and on drug dose adjustment in patients with renal impairment. A procedure is established in case of emergencies, e.g. if an important drug for a serious condition is not administered by the patient. If a patient reports difficulties with drug administration (difficulties swallowing tablets or capsules, tablet splitting, subcutaneous injections, use of inhalers, transdermal patch application, or with the administration of eye drops, nose drops, ear drops, or rectal or vaginal drug administration), specific information is provided to the patient.
Management of vascular risk factors	- Assessment of medication and diagnoses, lab values, health parameters, lifestyle factors, blood pressure and anthropometric measurements (height, weight) - Information on further vascular risk factors (e.g. smoking, medical history) - Feedback on vascular risk, importance of reducing the risk, and possible ways of achieving such a reduction - Nutritional counseling, recommendation of weight loss (if necessary), physical activity enhancement, and optimization of medication as described above

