*Self-reported impairments and symptoms*	Standardized questionnaire on self-reported impairment in walking, vision, or hearing [self-constructed items^c^] Standardized questionnaire on self-reported anticholinergic symptoms [self-constructed items^c^]
*Anthropometry, blood pressure*	Measurement of height, weight, blood pressure; calculation of body-mass-index (BMI)
*Nutrition*	Standardized questionnaire on food consumption (food frequency questionnaire/FFQ [59])
*Physical activity I*	Standardized questionnaire on physical activity [self-constructed items^c^]
*Bereavement, grief*	Standardized questionnaire on bereavement [60]
*Medication I*	(i) Information from the attending GP on participants’ medication (“GP-list”) and diagnoses^b^, lab values using GP practice records and (ii) information from participants on their actual medication (“brown-bag review”), adherence, and difficulties with drug administration using standardized questionnaires [self-constructed items^c^]
*additional vascular risks*	Standardized questionnaires on additional vascular risk factors (e.g. smoking, medical history, familial medical history; [self-constructed items^c^])
*Instruments to assess further information in intervention group A*	
Construct	Instrument
*Physical activity II*	Weekly records on conduct of the physical activity intervention component, training, and pedometer results [self-constructed items^c^]
*Cognitive training*	Weekly records on conduct of the cognitive training [self-constructed items^c^]
*Medication II*	Standardized feedback questionnaires on potential changes in a participant’s medication or reasons for not following the recommendations, completed by the attending GP [self-constructed items^c^]
*Social activity*	Weekly records on social activity, in addition to the information collected on social inclusion (see above)
*Motivation and readiness for change*	Standardized questionnaire on motivation and readiness for behavior change [55–57]
*Instruments to conduct the process evaluation*	
Construct	Instrument
*Success rate of recruitment and quality of the study population*	Standardized questionnaires filled out by the GP practice personnel (number of eligible GP patients, number of participants and non-participants, (baseline) characteristics of participants and non-participants, reasons for non-participation) [self-constructed items^c^]

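### SAE status is limited to three event types, so a death or lasting impairment arising outside them and without admission triggers no SAE notification

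*Protocol article*

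**What the plan says.** The Harms section works in three steps.

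- **What is recorded.** AEs "will be assessed without regard towards a causal relation to the intervention", at every participant contact after baseline. The categories "include loss experiences and grief, depressive symptoms, severe injuries, hospitalization, and private or occupational stress reported by participants".
- **What becomes serious.** "Specific AEs (depressive symptoms; severe injuries; hospitalization) will be considered serious adverse events (SAEs) if they result in a life-threatening condition", which the text expands in a parenthesis and continues: "immediate risk or death), hospitalization/prolongation thereof, or any lasting impairment".
- **What follows.** An SAE generates an automatic form to the coordinating centre. That centre contacts the study centre concerned, and the two jointly decide whether to inform the GP, interrupt or end participation, or do nothing further.

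Three other places bear on this. Under Data monitoring: "A data monitoring committee will not be established as the overall risk associated with the trial is considered low"; the same section then points the reader to precautions against harm set out further on. In Table 1 (Interventions), the medication component of group A states: "Reports including recommendations on the medication of a participant will be transmitted to the GP". In Table 2, mortality is a secondary endpoint obtained from the GP or a confidant, and the list of further information contains a "Standardized questionnaire on self-reported anticholinergic symptoms".

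**The concern.** Seriousness is normally a property of an event's outcome. Here an event must first belong to one of three named types, and only then is its outcome considered. Some events with the gravest outcomes can fail the first step.

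At stake is the notification, because it is the route the article describes by which a single serious event reaches the coordinating centre and prompts a decision. With no data monitoring committee, and with the Data monitoring section relying on precautions described later, the Harms rule carries much of the safety oversight. A between-group table of SAEs built on it would also leave out the same events.

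The AE list fits the intervention poorly as well. It names grief and occupational stress, but not suspected drug reactions or events during exercise. Group A receives recommendations on drugs through the GP, together with strength and aerobic training.

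**Working it through.** No figure in the article depends on this rule, so there is nothing to recompute. The check reads the definitions against each other.

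**Step 1: count the categories.** Five AE categories are listed: loss and grief, depressive symptoms, severe injuries, hospitalization, and private or occupational stress. Three can become serious (depressive symptoms, severe injuries, hospitalization). The other 5 − 3 = 2 (loss and grief; stress) cannot. Suspected adverse drug reactions are named in none of the five.

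**Step 2: is either list open?** The AE list is introduced by the verb include, so further events may be recordable as AEs. The SAE sentence has no such word; it names its three types in a parenthesis. An unlisted event could therefore be recorded as an AE and still have no route to SAE status.

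**Step 3: run cases through the rule.**

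| Event | One of the three types? | Meets a listed outcome? | SAE as written? | Seen elsewhere? |
|---|---|---|---|---|
| Medical event or drug reaction leading to admission | Yes (hospitalization, any cause) | Yes | Yes | – |
| Severe injury with lasting impairment, no admission | Yes | Yes | Yes | – |
| Sudden medical death at home | No | Yes (death) | **No** | Mortality endpoint |
| Disabling drug reaction managed without admission | No | Yes (lasting impairment) | **No** | Partly, if its symptoms are anticholinergic |

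The last two rows are the gap: the outcome criterion is met and the type criterion is not.

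**Step 4: hospitalization in both roles.** It is an event type and also a seriousness criterion. Read literally, every admission satisfies the condition by being an admission, so the condition filters nothing. Read otherwise, an admission needs something more, such as prolongation, a threat to life or lasting impairment. The two readings give different SAE counts from the same events, and the text does not choose. The first row of the table rests on the literal reading.

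**Step 5: fit to the medication component.** The rationale in the Objectives section describes inappropriate medication as "leading, for example, to an increased risk of adverse drug reactions, hospitalization, and mortality". Table 1 has recommendations on inappropriate, possibly missing and contraindicated drugs sent to the GP. Table 2 follows these up with GP feedback on changes made or reasons for not making them; no adverse-reaction item is stated there. The Harms section does not name such reactions either.

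**The case against.** The case on the other side is substantial and narrows the point in several ways.

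- **Admissions are caught whatever their cause.** AEs are recorded without a causality judgement and hospitalization is a listed type. Cardiac events and drug reactions that lead to admission are therefore inside the rule. Severe injury, an obvious risk of exercise, is inside too. This stands. A reader might infer that the rule cannot reveal harm from the medication or exercise components; the text does not support that.
- **Deaths are counted.** Mortality is a secondary endpoint, so a death at home enters the comparison between groups. This stands. What is missing is the SAE notification, not the count. No notification or review is stated for deaths that reach the trial only through endpoint collection.
- **Drug reactions are not wholly uncollected.** The AE list need not be exhaustive, anticholinergic symptoms are asked about, and reactions leading to admission enter as hospitalizations. A reader might conclude that adverse drug reactions are not collected at all. The article supports only that they are not named as an AE category.
- **The rationale should not be over-read.** Adverse drug reactions appear there as one example of what existing inappropriate medication can cause, a harm that the component aims to reduce. They are not presented as a main reason for the component. Likewise, the low-risk statement under Data monitoring is a judgement made in advance, not a conclusion to be drawn from SAE counts.
- **Other safeguards exist.** Recommendations go through the GP with information on interactions and renal dosing, an emergency procedure is mentioned, and conditions affecting safe engagement are exclusion criteria. These lower the expected number of events but do not change how an event is classified.
- **A journal article is condensed.** Form layouts and detailed event lists may well sit in the full protocol. That answers a complaint about missing detail. It does not answer this one, because the article states a specific closed rule, which a fuller document would have to contradict in order to repair.

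**Conclusion.** The point holds in a bounded form. As written, a death or lasting impairment that arises outside depressive symptoms, severe injury and hospitalization is not an SAE and does not start the notification and joint decision. The gap is confined to events without admission. The double role of hospitalization leaves the SAE count open to two readings, and suspected drug reactions are not named as an AE category despite the medication component.

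The size cannot be given, because the article states no rates for deaths outside hospital or for impairment managed without admission. The number of affected events may be small. The point is worth acting on because the excluded events include deaths and the correction is cheap.

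The conclusion assumes that the SAE sentence means what it says, with its parenthesis a closed list, and that hospitalization is read literally so that every admission qualifies. If the second assumption fails, the gap is wider.

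**What to change.** 1. Define an SAE by outcome for **any** AE: death, life-threatening condition, hospitalization or its prolongation, or lasting impairment.
2. Use hospitalization as a criterion only, and record the event that led to the admission as the AE.
3. State that every death is notified as an SAE, including deaths first learned of through the mortality endpoint.
4. Name suspected adverse drug reactions and exercise-related events in the AE list, and ask about them in the same words in both groups.

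This changes a reporting definition and leaves clinical management as it is. It costs a reworded paragraph, a few fields in the existing electronic form, and somewhat more notifications for the coordinating centre to process.

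One caution on item 4: identical wording does not make ascertainment equal. AEs are recorded at each contact, and the Data collection section schedules six interim contacts (months 2, 4, 8, 12, 16 and 20) for group A only. With the 24-month visit, that makes 6 + 1 = 7 scheduled contacts after baseline in group A against 1 in group B. Comparisons of AE counts between groups should be read with that in mind.
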